#### Inclusion/exclusion criteria

Extremely premature infants are eligible for the study if they meet the following inclusion criteria: birth weight < 1250 g; mother plans to pump and provide milk for at least 2 months; absence of severe congenital anomalies; NICU admission ≤ 24 hours of life; ability to begin protocol within 96 hours of life. The exclusion criteria are as follows: birth asphyxia (cord pH/arterial pH < 7.0); presence of a tracheoesophageal fistula, maternal + HIV status, maternal drug or substance use that precludes infant from receiving mother’s milk, triplets or higher order multiple births.

#### Participant recruitment, enrollment and informed consent

The collaborating sites have a relatively high census of extremely premature infants yearly and very high lactation initiation rates (80–90 %) which facilitates subject recruitment. Mothers on bed rest protocols in the high risk antenatal unit, who meet inclusion criteria (estimated fetal weight < 1250 g per prenatal ultrasound) are approached and invited to participate. In our pilot studies, this recruitment strategy was highly successful and the majority of women approached agreed to participate. Mothers who deliver without significant time in the antenatal unit are approached within 96 hours after delivery.

The principal investigator (PI) and/or research nurse explain the study in detail, answer questions, and leave the consent form so that the mother can read it and discuss the study with her family prior to enrolling. A second meeting is scheduled later that same day, when convenient for the mother, and the PI and/or research nurse return and answer any additional questions. Informed consent is obtained at this time (second meeting) if the mother decides to participate. This precaution is taken because these women are considered psychologically vulnerable, in terms of research. Mothers are informed that their care (or their baby’s care) will not be affected if they decide not to participate in this study. In addition, mothers are informed that they have a right to withdraw their infant (or themselves) from the study at any time and for any reason without compromise to their care, or their infant’s care.

If the woman is approached antenatally, before securing informed consent, the PI and/or research nurse explain to her that if she remains pregnant and the estimated fetal weight (EFW) is over 1250 g per prenatal ultrasound, then the infant, once born, will no longer qualify for the study. This is deemed a screen failure since the infant will no longer meet inclusion criteria. All women are assured that their infant’s care, and their breastfeeding support post-birth, will not be affected by their decision to participate in the study, or if they become ineligible. Since 27 % of enrolled mothers are expected to be Hispanic, Spanish-IRB-approved translations of study documents are available at all sites.

#### Randomization

A 1:1 blocked randomization scheme was utilized to yield “comparable” subjects in each of the 2 groups, stratified by birthweight (<750 g, 751–999 g, 1000–1250 g) within each site, to avoid imbalance in the distribution of the 2 groups at each site. We produced a separate block randomization list within each site for each subgroup (a total of three strata). The randomization is based on permutated blocks with random sizes varying from 2 to 4 (to avoid guessing) to make sure that each site will have an equal number of participants in each group. The randomization list was generated prior to study initiation using a random seed number via SAS PROC PLAN (SAS Inc., Cary, NC, USA) to generate the stratified randomization design. The statistician prepared sealed, numbered opaque envelopes for each site, with randomization assignment inside. The envelopes were given to the site’s research coordinator who assures that they are used in numerical order. After informed consent is obtained, the research coordinator opens an envelope, removes the group assignment form, writes the infant’s study ID # and date on the form, makes a copy of the form and sends it to the statistician, keeping the original in the infant’s study file. Group A (treatment) infants receive OMM, while Group B (control) infants receive a placebo (sterile water). In the case of a multiple birth, twins are stratified and randomized into either the intervention or the control group, and will be analyzed independently between the two experimental groups. Triplets or higher order multiple births are not be eligible for the study.

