## Methods/Design

### Study design

This study is a 5-year, prospective, double-blind, placebo-controlled randomized clinical trial across 5 large neonatal centers, designed to evaluate the safety and efficacy of oropharyngeal administration of own mother's milk to reduce the incidence of L-OS, and NEC and death, in a large cohort of extremely premature infants (*n* = 622; total patients enrolled). A multi-center 5-year trial is necessary in order to reach the target sample, based on average numbers of extremely premature infants admitted yearly to participating sites. Enrolled infants are randomized to one of 2 groups using computer-generated random numbers: Group A (treatment) infants receive 0.2 mL of own mother’s milk (OMM) via oropharyngeal administration every 2 hours for an initial treatment period of 48 continuous hours, followed by an extended treatment period of 0.2 mL of OMM via oropharyngeal administration every 3 hours until 32 weeks CGA. Group B infants (control) receive a placebo (sterile water, and blinded as described below) using the same dose and following the same protocol. Samples of mother’s milk and infant’s urine are collected at baseline and within 6 hours after the completion of the Initial Treatment Period and the Extended Treatment Period. A sample of infant’s urine is collected at 7 days of life. Milk, oral mucosal swab, and stool samples are collected at the time of first stool, 2 weeks of life and at 32 weeks CGA. For infants diagnosed with L-OS or NEC, a stool sample is collected at the time of diagnosis. Health outcome and safety data are closely monitored and collected throughout the infant’s stay until discharge or death. See Fig. 1 for the timeline of the study.

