#### Study approval

The study was approved by the Institutional Review Board (IRB) at the NorthShore University HealthSystem (primary site) and by the IRBs at the New Hanover Regional Medical Center and the St. Joseph’s Regional Medical Center. Subject enrollment is in progress at these three study sites. Recruitment at the Advocate Children’s Hospital and also the Morristown Medical Center study site will not begin until IRB approval has been obtained. All investigators, treating physicians and nurses, project director, data analyst, and lab technicians are blind to group assignment, except the (site) research nurse who assigns subjects into groups and prepares syringes.

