#### Study procedures

##### Collection of milk

Research personnel within each site have been trained, using a standardized protocol (Protocol version 4; Dated 1/5/2015), to assure coherence of data collection. Mother’s milk samples are collected during the routine expression of milk, using a hospital-grade electric breast pump, and are stored in the NICU breastmilk refrigerator. When at least 2.5 mL (½ teaspoon) of mother’s milk is available, the research nurse prepares the syringes for the first 24 hours of the Initial Treatment Period. For infants in the placebo group, the milk is immediately frozen, in a separate NICU breastmilk freezer to maintain blinding, for later use when enteral feedings are started. Using sterile gloves, 24 sterile oral syringes are each filled with 0.1 mL of OMM or sterile water (based on group assignment), capped, and covered with a white tape as a blinding procedure. Each syringe is labeled with the patient’s name, medical record number, and the date and time of preparation. Syringes are prepared in the same sterile manner, by the research nurse, every 24 hours. For the Extended Treatment Period, a total of 16 syringes are prepared daily, for treatments to be given every 3 hours.

It is standard practice to encourage mothers of extremely premature infants to pump frequently (typically every 3 hours) in order to establish and maintain an abundant milk supply. Therefore, it is common for NICU nurses to see several containers, with varying amounts of mother’s milk, in the NICU refrigerator, on a daily basis. The milk is either used for enteral feeds or frozen for storage. Since only miniscule volumes of milk are needed daily for this intervention (2.4 mL and 1.6 mL per day, for Initial and Extended Treatment Periods, respectively) it has been our experience that NICU nurses do not notice that a small volume of milk has been removed from the refrigerator, and thus they remain blind to group assignment.

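### The plan lets the unblinded research nurse take consent, and blocks of 2 or 4 do not stop that person guessing the next allocation

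*Protocol article*

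**What the plan says.** Four sections of the protocol article bear on this.

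- **Study approval.** Investigators, treating staff, the data analyst and laboratory staff are blind, "except the (site) research nurse who assigns subjects into groups and prepares syringes".
- **Collection of milk.** The same role fills the milk or water syringes throughout treatment: "Syringes are prepared in the same sterile manner, by the research nurse, every 24 hours".
- **Participant recruitment, enrollment and informed consent.** The study is explained at a first meeting. At a second meeting that day, "the PI and/or research nurse return and answer any additional questions. Informed consent is obtained at this time". Mothers may be approached before birth or within 96 hours after delivery.
- **Randomization.** "A 1:1 blocked randomization scheme was utilized", stratified by three birth-weight bands within site, using "permutated blocks with random sizes varying from 2 to 4 (to avoid guessing"). Sealed, numbered, opaque envelopes are used in order. After consent, "the research coordinator opens an envelope, removes the group assignment form", and the original form stays in the infant's study file.

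The section on study approval gives assignment to the research nurse, whereas the section on randomization gives envelope opening to the research coordinator. The article does not say whether these are the same person.

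**The concern.** Sealed envelopes hide the next form. They do not hide what can be inferred from the forms already opened. Inference is easy when blocks are short and the observer knows the past allocations. The one role that has this knowledge is also allowed to recruit.

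Foreknowledge matters only if it can influence who enters, and here it has some room to do so. One eligibility criterion is the mother's intention to pump for at least two months, which calls for judgement. The sample-size section expects substantial refusal: 1270 screened × 0.70 = 889 mothers providing milk, of whom 30% (about 267) decline. Whom to approach, and how persuasively, could therefore follow the expected arm. Blinding after allocation does not protect against this. Stratification and adjustment for sex, gestational age and birth weight would absorb part of such selection, but not selection on illness severity that is not in the model.

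**Working it through.** The article gives no predictability figure, so there is none to reproduce.

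**Inputs**
- Ratio 1:1 (Randomization).
- Block sizes 2 and 4 (Randomization). A block of 3 cannot be balanced at 1:1.
- Mix of sizes: not stated. Equal probability is assumed, and the range is shown.
- Lists: "We produced a separate block randomization list within each site for each subgroup (a total of three strata"), and the trial runs "across 5 large neonatal centers", so 3 × 5 = 15 lists of about 622/15 = 41 infants.
- Past allocations: known to whoever assigns infants and prepares syringes.

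**Guessing rule.** Guess the arm that is behind in the list, and toss a coin when the arms are level. Every complete block is balanced, so the running imbalance in a list equals the imbalance within the current block. The observer need not know where blocks begin.

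**Expected correct guesses in a block of size 2m:** m + 2^(2m−1)/C(2m,m) − 1/2
- Size 2: 1 + 2/2 − 0.5 = 1.5, and 1.5/2 = 75.0%.
- Size 4: 2 + 8/6 − 0.5 = 2.833, and 2.833/4 = 70.8%.
- Equal mix: (1.5 + 2.833)/(2 + 4) = 72.2%.
- 25% blocks of 2: (0.375 + 2.125)/(0.5 + 3) = 71.4%.
- 75% blocks of 2: (1.125 + 0.708)/(1.5 + 1) = 73.3%.

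Any mix lies between 70.8% and 75.0%. A simulation of 622 infants in 15 lists with an equal mix gave 71.8%.

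**Certain allocations.** A lead of two arises only when a block of 4 opens with two equal allocations, which has probability 2/6 = 1/3. The third and fourth are then fixed. With an equal mix this is (1/3 × 2)/(2 + 4) = 11.1% of allocations; simulated 41-infant lists gave 10.6%. This share depends on the mix: 0.75 × (2/3)/3.5 = 14.3% with 25% blocks of 2, and 0.25 × (2/3)/2.5 = 6.7% with 75%.

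**Other recruitment situations**
- Antenatal consent, weight band not yet known: a simple guess from the three lists of the site was right about 63% of the time in simulation, assuming the bands are equally likely. Randomizations between consent and birth are not allowed for and would lower it.
- Blinded investigator recruiting without the nurse: 50%.

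**Larger blocks.** Size 6 gives 3 + 32/20 − 0.5 = 4.1 correct, and size 8 gives 4 + 128/70 − 0.5 = 5.329. Sizes 4, 6 and 8 equally likely give (2.833 + 4.1 + 5.329)/18 = 68.1%; simulated 41-infant lists gave 67.3%.

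**The case against.** The strongest reply is that the overlap is allowed but not shown. A site may have several research nurses, the coordinator may be someone else, and delegation of duties is often left to the full protocol or a site manual. It stands that the article does not say one person does everything. The objection does not dispose of the point, because the article does state who recruits and who is unblinded, and its wording admits the same person. If the coordinator is someone else, the nurse still learns the allocations from the syringes.

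Three further objections stand in part.
- **The 72% is conditional.** It counts coin tosses at ties as half right. It needs the unblinded nurse to recruit after birth, know the stratum and have followed its list. The number of lists does not enter the calculation.
- **The antenatal route weakens foreknowledge.** Stratification is by birth weight, and the recruiter does not choose the time of birth. The long approach window is not an aggravating feature.
- **Discretion is limited.** Most eligibility criteria are objective, the second meeting is later the same day, the envelope is already opened only after consent, and the primary model adjusts for three prognostic factors.

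A reader might infer that recruiters in this trial generally predict 72% of allocations, or that the comparison is biased by some number of percentage points. The document supports neither. It does not say how often the nurse recruits, and any bias figure would need assumed sepsis risks for infants enrolled under each guess.

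**Conclusion.** The point holds as a gap in allocation concealment that the written roles permit. For the unblinded nurse, varying the block size between 2 and 4 does not achieve its stated purpose. When that nurse recruits after birth with the stratum known, the best guess is right about 71–75% of the time, against 50% with no information. With equally likely sizes it is 72%, and about 11% of allocations are certain. The size of any resulting bias is unknown, and nothing in the article shows that selection has occurred.

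The correction is worthwhile because it is cheap and most allocations lie ahead. The discussion section reports 77 enrolled less 11 screen failures, or 66, so (622 − 66)/622 = 89% of the target remained when the article was written.

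**What to change.** In the sections on study approval, recruitment and consent, and randomization, state that anyone who opens envelopes or prepares syringes does not approach mothers, judge eligibility or take consent. Assign those tasks to a blinded site investigator or to other blinded study staff already in place. Investigators are already declared blind, and site PIs are mentioned in the safety and data-management sections. Use one name for the person who opens envelopes, or say how the nurse and coordinator differ. Require eligibility and birth weight to be entered in REDCap, which all sites use, before the envelope is opened; consent already comes first.

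The cost is a role rule in the manual and site training, and less flexible scheduling of consent meetings. Treatment, endpoints and sample size do not change.

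Larger mixed blocks are optional and secondary. Sizes 4, 6 and 8 lower the best guess only to about 67–68%, with slightly more possible imbalance in small strata. They suit only lists whose envelopes have not been used. The list was generated before study initiation, so the lists of the two sites awaiting ethics approval should not be assumed unissued.

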##### Data management and quality control

The goals of data management are: (a) to ensure that data collected across sites are properly and accurately entered and documented; (b) to ensure that data will be stored in an electronic format that will allow the primary investigators of the project to retrieve data easily and to export data to statistical packages; and (c) to ensure the confidentiality of subjects. Prior to data collection and entry, a standard codebook was created which contains the variable names, descriptions, and value codes of each variable/item collected within each site. Following development of the codebook, a web-based SQL (Structural Query Language) data capture and archiving system was created using REDCap to standardize data collection across the five study sites. The web-based REDCap application, developed by Vanderbilt University, offers intuitive design and tailored clinical research workflows that enable research team members across collaborating study sites to share, capture and manage data. REDCap provides secure user-friendly web-based case report forms, real-time data entry validation (e.g. for data types and range checks) and audit trails. Users from different sites can be assigned different levels of access which can be form or rights based. All data are stored in the password-protected network server at NorthShore with back-up scheduled at every midnight. The original raw data within each site is stored in a locked cabinet accessed only by key project personnel. For quality control, we have developed and implemented standard protocols for data collection and enrollment monitoring across study sites. We have also implemented communication systems and documentation of study-related plans, decisions, progress, and analysis management for efficiently throughout all phases of the research. All research personnel within each site have been trained using a standard protocol. The training covers areas such as recruiting, enrollment, randomization, and web-based data collection.

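### The randomisation steps reveal the arm before the assignment form is tied to an infant, leaving a small untraceable gap for infants pending together, mainly same-stratum twins

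*Protocol article*

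**What the plan says.** All of the procedure stands in the protocol article, Methods/Design, Randomization.

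- **List.** "The randomization list was generated prior to study initiation using a random seed number via SAS PROC PLAN". There is a separate list for each of three birth-weight strata within each site, allocation is 1:1, and block sizes vary from 2 to 4.
- **Device and custody.** The statistician made up a set of envelopes for each site; they are sealed, opaque and numbered. Custody and order of use rest with one person at the site: "The envelopes were given to the site’s research coordinator who assures that they are used in numerical order".
- **Moment of allocation.** "After informed consent is obtained, the research coordinator opens an envelope". In full, the coordinator's steps are: "the research coordinator opens an envelope, removes the group assignment form, writes the infant’s study ID # and date on the form".
- **Record kept.** The coordinator "makes a copy of the form and sends it to the statistician, keeping the original in the infant’s study file".
- **Twins.** "twins are stratified and randomized into either the intervention or the control group". Triplets and higher-order births are excluded.

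The section does not say when the study ID is issued, or whether the infant is entered in a log or on the envelope before it is opened.

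**The concern.** Concealment by envelope depends on committing a particular infant to a particular envelope before anyone sees what is inside. In the order printed here, the commitment on the form comes after the assignment has been read. With only one infant waiting, this hardly matters: consent is already given and the next envelope is fixed. With two infants waiting in the same site and stratum, the person holding the envelopes can learn one or both arms and then decide which infant's ID goes on which form.

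Same-stratum twins are the natural case, because both can be eligible and consented at the same time. Nothing in the section says which twin takes the lower-numbered envelope. If the choice followed prognosis, the comparison of late-onset sepsis, necrotizing enterocolitis and death would carry some selection bias.

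This differs from guessing the next allocation from short blocks. Here the actual assignment is in view.

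**Working it through.** The plan states no figure on this point, so there is none to reproduce. The check has three parts.

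**1. What the described records could reveal**

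The records are the pre-generated list, the envelope numbers, the dated forms carrying an ID, and the statistician's copies.

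- *Envelope skipped or used out of order.* The numbers and dates on the returned forms would not run together. This is visible.
- *Opened envelope held back for a later infant.* The infant at hand then takes a higher number on an earlier date, or has consent but no allocation. An altered date could be compared with consent and dosing dates. This is often visible.
- *Two infants of one site and stratum pending together, next envelopes k (milk) and k+1 (placebo).* Whichever ID goes on whichever form, both envelopes are used in order, both after consent, both forms can bear the same date, and both arms agree with the list. The records are the same either way, so the exchange is not visible.

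Only the third case escapes the records. It requires two infants waiting together and two envelopes with different arms.

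**2. How often infants could overlap**

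Inputs: 622 infants, 5 sites and 5 years (Study design); 3 strata per site (Randomization); protocol to begin within 96 hours of life (Inclusion/exclusion criteria). Assumptions: equal spread over lists, and steady, independent arrivals.

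- Infants per list: 622 / (5 × 3) = 41.5
- Per year: 41.5 / 5 = 8.3, or one about every 52 / 8.3 = 6.3 weeks
- Chance that the next infant on the same list arrives within 4 days: 1 − exp(−8.3 × 4 / 365) = 1 − exp(−0.091) ≈ 9 %

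Overlap of unrelated infants is therefore uncommon. Twins break the independence assumption and are the main case. The document gives no expected share of twins.

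**3. Size of a bias, if steering occurred**

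Inputs: 249 per arm (Sample size/Power analysis). Assumptions with no source in the document: sepsis risk of 15 % in both arms (midway between the planned 10 % and 20 %), a share s of infants in pairs whose arms are decided by prognosis, always in the same direction, and a risk gap d within those pairs.

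- SE of the risk difference = √(2 × 0.15 × 0.85 / 249) = 0.0320, or 3.2 points
- Bias = s × d
- Type I error = P(|Z + s × d / SE| > 1.96), two-sided, unadjusted comparison

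| s | d | Bias | Type I error |
|---|---|---|---|
| 5 % | 15 points | 0.75 points | 5.6 % |
| 10 % | 15 points | 1.5 points | 7.6 % |
| 20 % | 15 points | 3.0 points | 15.5 % |

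Only the product s × d matters. Halving the gap to 7.5 points at s = 10 % gives 0.75 points again, and so 5.6 %.

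**The case against.** The strongest reply is that a journal article condenses a full protocol, here version 4, which is not shown. An entry on the sealed envelope or an opening log is the sort of detail left to that document. The article also says of site staff: "The training covers areas such as recruiting, enrollment, randomization, and web-based data collection". This stands in part. The absence of a log from the article is no finding. But the order of opening the envelope and completing the form is stated, not omitted, and as stated it shows the arm first.

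Three stronger readings are tempting, and the document does not support them.

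- *The infant's ID is on nothing before the envelope is opened.* The article says only when the ID goes on the form. An ID or log entry may already exist.
- *No record could ever show misuse.* The list, the numbered envelopes, the dated copies and the audit visits described under Data management and quality control could reveal skipped envelopes or dates that do not fit. Only an exchange between infants pending together escapes the allocation records.
- *Concealment fails by procedure and no analysis could help.* Opening after consent closes the main route, which is deciding on enrolment with the arm known. The primary model adjusts for sex, gestational age and birth weight, so steering on those factors would be partly corrected. Steering on unmeasured bedside severity would not.

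The assumed magnitudes are also open to attack. A 15-point gap around a mean of 15 % means 22.5 % against 7.5 %, a threefold difference within one birth-weight stratum, judged in the first days of life. The largest figure further needs one infant in five to be steered, always the same way. That criticism stands, and the table shows only what such values would imply.

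**Conclusion.** The point holds in a limited form. The printed sequence lets the coordinator see the allocation before the assignment form is tied to an infant. The stated safeguards confine the untraceable consequence to infants pending together in one site and stratum, mainly twins.

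The document shows no breach and gives no basis for estimating how often one might occur. On assumed values the effect is small when few infants are affected (0.75 points of bias and 5.6 % type I error at s = 5 %) and becomes serious only under assumptions that are hard to defend. This is a minor weakness with a nearly free remedy.

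**What to change.** Reverse the two steps.

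1. Before opening, write the infant's study ID, stratum, date and time on the sealed, numbered envelope and on a site log sheet, or register the infant in REDCap. Count the infant as randomised from that entry.
2. For twins in the same stratum, assign the lower-numbered envelope to the first-born, and record this before opening either envelope.
3. If the full protocol already records the infant before opening, correct the description in the Randomization section instead.

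A paper log is kept by the same coordinator who holds the envelopes, so it mainly deters and documents. The REDCap route adds an audit trail outside that person's hands, and the system is already in use across the sites.

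The cost is one line in the procedure and a log sheet per site, with no extra infants or staff. The change would still cover most allocations. The Discussion reports 77 enrolled, of whom 11 were screen failures, leaving 66 against a target of 622 (66 / 622 = 10.6 %), and two of the five sites had not begun recruiting.
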